### Trial process

Women who are interested in taking part in this study will contact a RA by telephone. The RA will review the study purpose with each woman, assess her eligibility using a Recruitment and Eligibility Form, and invite all eligible women to participate. Initially, the RA will obtain informed verbal consent by reading the letter of information to the woman and answering questions she may have; as noted below, women will provide written consent to participate when they login to the website. Each woman who consents will have her name, safe email address and preferred contact information, province of residence, whether she has children or not, and how she learned about the study recorded on the Eligibility and Recruitment Form by the RA. The RA will discuss safety concerns with the woman and develop a plan for safe contact with the study. The RA will also enter this information into an electronic tracking database, housed on a secure server at The University of Western Ontario. The woman will then be asked to create a security question and answer for the purpose of identification in the case of a lost password.

Entry of the woman’s safe email address into the tracking database will initiate her enrollment into the study. At this point, the system will generate a unique study ID, randomly assign the woman to either the intervention or control group, and send out an automated ‘welcome’ email to the woman’s safe email address containing a link to the letter of information and consent, and a corresponding URL, username and password. The women will be instructed to use these credentials to login to the website. The first time the woman logs into the website, she will be asked to re-affirm her consent to participate by selecting 3 radio buttons indicating that: a) she has read the letter of information, b) has had all questions about the study answered, and, c) agrees to participate. These questions must be answered affirmatively in order to proceed.

At baseline, the woman will be encouraged to login and complete the baseline measures and intervention activities on the same day she is randomized and receives her study website password. The woman will be allowed to complete the baseline study visit in more than one sitting; completed responses will be automatically saved so that the woman can continue where she left off when she logs in at other times. However, she will have 6 weeks from the time of enrollment in which to complete the baseline measures and accrue to the trial. Automated and manual emails will be sent at regular intervals over the 6-week period until the woman either completes baseline measures or the time expires. Should the time expire, an email message will be sent to inform the woman that she is no longer able to complete the tool. Based on the IRIS trial and our pilot study, baseline study measures are expected to take about 30 min to complete. The additional time required to complete intervention activities is 30-60 min for women in the intervention arm and 20-30 min for those in the control arm.

For 3, 6 and 12-month follow-up, automated reminder emails will be sent to the woman’s safe email address notifying her that she is due to complete another session. The woman’s username and password, along with the study URL will be included in the email notification. When the woman returns to the website, the study measures will be slightly different for the 3, 6 and 12 month assessments. At these follow-up visits, women in the intervention group will be invited to complete the intervention activities again if they wish, and encouraged to consider this option if their situations have changed. Once enrolled, women will be able to visit their assigned website between scheduled study visits to review their responses. Women in the intervention arm will be able to update some activities, such that the online tool can be used as an ongoing resource that changes and evolves to fit with their changing life contexts (see Intervention arm for details).

Website utilization data for both study arms will be collected automatically to: 1) track the number of times the site is accessed within scheduled follow-up windows and between windows; 2) the time spent on a session and within specific sections; 3) item completion rates; and, 4) materials accessed and skipped. This information will be used to describe the how women engage with the intervention and control websites as well as inform us on dosing.

### Online Interventions

The online interventions that will be delivered to women in both arms are organized into the same sections and focus on: 1) questions about women’s background characteristics; 2) women’s plans for their relationship with their abusive partner, their priorities and current safety risks; 3) an action plan containing safety planning information and resources, and 4) a structured debriefing. The content of each section by study arm is summarized in Table 1, with details of each provided in the text that follows.

**Table 1 Tab1:** Comparison of content of intervention and control arms

Section	Study arm		Study arms differ
	Tailored intervention	Usual care control	
Background questions	Questions about women’s demographic characteristics and living situation	Questions about women’s demographic characteristics and living situation	No
My decisions, priorities, risks	• Plan for Relationship • Priorities Exercise with personalized feedback • Danger Assessment with personalized feedback	• Plan for Relationship • General Information about Priorities • General Information about risk of IPV	No Yes Yes
My action plan	Strategies organized in 8 categories with associated resources • Recommended based on her responses to questions and activities; woman can further customize	Emergency safety planning and child safety strategies and resources • General information not personalized to the woman’s situation; no opportunity to modify	Yes
Debriefing	Standardized information about symptoms of a stress reaction and strategies for managing	Standardized information about symptoms of a stress reaction and strategies for managing	No

#### Intervention arm (tailored, online safety and health intervention)

Women will initially respond to questions about their personal context (such as whether they have children, are employed, were born in Canada). In the next section, “*My Decision, My Priorities, My Risks*”, women will complete a series of questions and interactive activities. First, women will be asked to reflect on their relationship with their abusive partner and to report on their current plan from 5 options (i.e., stay with partner, separate, remain separated, return to partner, unsure). Second, women will be invited to complete an interactive priority setting exercise in which they will rate the relative importance of 5 factors (my feelings for my partner, my health and well-being, having resources, my concern for safety, and my children’s well-being) in making decisions about their unsafe relationship. Women will be shown pairs of priorities positioned at opposite ends of a horizontal line and then slide a toggle bar toward the priority that is more important to them. Weights for each priority will be computed mathematically and real time feedback provided in the form of a graph, along with examples of safety strategies in the action plan that fit with the top priority identified. Third, women will complete the Danger Assessment (DA), or DA-Revised (for women with partners other than men), a validated risk assessment [36, 37]. Using the DA, women will be asked to mark the type and timing of episodes of physical and/or sexual violence from their partner in the past 12 months on a calendar, and then respond to 19 questions assessing risk factors for serious or lethal violence. A standardized weighted score (range 0-38), calculated using these responses, will then be provided to the women on a graph with information about the corresponding level of risk, ranging from variable danger to extreme danger, and a brief personal message about their level of danger and suggested actions.

Next, in “*My Action Plan”*, women will create a tailored Action Plan for themselves by selecting from 46 strategies organized in 8 different groups (Emergency Plan; Domestic Violence Information and Services, Security Measures, Basic Resources, Health, Support from Family, Friends and Community, Child Safety and Legal Strategies). Each strategy conveys detailed information about actions women could take to address their safety and health concerns. To engage diverse groups of women, these strategies are intentionally written in a conversational tone, use a coaching approach that includes ‘tips’ for accessing services (e.g., how specific services work and how to access them more quickly) or using a strategy (e.g., a guided video to demonstrate grounding exercises), and comments about conditions that might alter the strategies (e.g., If you live in a rural community…..”). Linked resources include contact and other information for services, and relevant websites and videos. When women begin this exercise, some strategies will be marked as recommended for each woman based on her unique responses to previously completed questions and activities (e.g., whether parenting children, plan for the relationship, DA score). Women will be instructed to select each strategy to open and read it, and to further personalize their action plan by selecting additional strategies important to them, and/or removing (de-selecting) those which they do not want to keep in their plan. Encouraging customization by the woman is an approach that reinforces her control in creating the plan. Women will be encouraged to save, print or access the Action Plan online at any time if safe to do so, and to visit the website to update their Action Plans should their circumstances change.

As the final step in the intervention, women will be provided with information about the signs of a stress reaction, advised that this is a normal reaction that may occur following a study visit, and provided with suggestions for managing this type of reaction, if it occurs. This is part of a standardized debriefing protocol we have used successfully in other studies [38] and an important step in promoting women’s emotional safety when engaging with the study.

#### Control arm (General Online Risk and Safety Planning Information)

Women in the control arm will complete the same background questions and question about their plans for the relationship as those in the intervention arm. However, in Section 2, which focusses on decisions, priorities and risks, brief general information will be provided about the importance of considering priorities when making important decisions along with risk factors for IPV, but women will not complete the interactive Priorities Exercise or the DA, or be provided with individualized feedback. Next, women will be provided with an Action Plan containing emergency safety strategies (1 of 8 categories of strategies provided to the intervention group), including safety of children, and some general information about online and community resources that is not tailored to the woman’s situation. The type of information included will be consistent with what women would find online if they did their own search. In this sense, it constitutes a proxy for usual care. As with the intervention group, women will be able to save or print their plan for later use, or revisit the website at any time during the 12-month period of the study. After the final study visit has been completed, women in the control group will be offered an opportunity to complete the tailored, online intervention and provided with a clickable link to access it if they wish.

### Retention

We will use a retention protocol based on proven techniques for tracking women in longitudinal IPV studies [25]. Retention strategies will include: a) asking women for names and contact information for up to 6 people (family, friends, employers, service providers) who would know of their whereabouts and could be used as alternate safe contacts, along with their consent to contact people to release this information to us, b) contacting participants mid-way between the 4 study visits (at 1.5, 4.5, and 9 months post baseline) to confirm contact information and any anticipated changes to this; c) providing a small incentive for completing each of the 4 study visits, with the value increasing over time (i.e., $20, $30, $40 and $50); and, d) after each email or telephone contact, providing the woman with the name of the local RA, the study phone number and email, and the date of the next study visit. Efforts will be made by the RAs to use friendly, warm communication strategies to establish rapport with participants. It is hoped that by using telephone-based enrollment, women will feel more comfortable with the research team, and be more likely to ask for support if needed, improving retention.

### Safety and security

The physical and emotional safety of women who participate in the *iCAN* Plan 4 Safety trial is a primary concern. We will adopt many safety procedures used in the IRIS trial [19] with success (i.e., that trial reported no adverse events). All research staff will be trained in the use of these safety procedures. We expect the most significant safety risks faced by women in the trial will be from an abusive partner who becomes angry if they discover that she is participating in this research. A number of strategies will be used to prevent risk of detection by abusive partners and to ensure that participation is private and confidential. Information will be provided to all participants regarding the safe (private) use of computers and the Internet. As necessary, the RA will help the woman brainstorm a safe location to assess a computer or tablet (e.g., family, friend, public library, community agency, work, etc.). Women will be encouraged to not use a computer or tablet where the partner could potentially witness her participating in the study or access her Internet history. The RA will also offer training to the women about how to safely use the Internet. For example, the RA will provide information about deleting browser history and send this information to women via email if requested; this information will also be posted on the home page of the study website. When women load the *iCAN* website, a pop up dialogue box appears with information and instructions for opening the site in private mode (Incognito mode). The website is also equipped with a ‘quick escape’ bar that when clicked, leads to two actions: 1) provides immediate exit from the website and brings the user to the Google homepage; 2) pushes the tab running *iCAN* to the weather network webpage. All manual and automated emails sent to participants are addressed with the subject header “Women’s Health Study” to further reduce risk of detection.

Given the potential for questions about sensitive topics to trigger women with experiences of violence and trauma, and their experiences of stigma and judgment by others, women’s emotional safety was also considered in developing both the online surveys and the interventions to limit any potential emotional harms of participating. The language and content of the surveys and intervention was carefully drafted and reviewed to ensure inclusiveness and applicability to women from various backgrounds so that women could see themselves in the study, and to avoid phrasing that could be interpreted as blaming or stigmatizing. To increase women’s sense of comfort, we attempted to use an informal, conversational tone, included messages that acknowledged when questions or activities might create distress for women, and encouraged women to take a break if needed or otherwise care for themselves. As previously noted, we added a structured debriefing at the end of each study visit to remind the woman that she might experience a stress reaction after the session, that this is a normal response and to provide options for managing it.

Risk of suicidality is heightened in women with histories of IPV [39]. Although we do not anticipate that study participation will increase this risk, we adapted a protocol developed for the IRIS study for use in both study arms. Safety programming has been integrated into the online interventions to: a) identify women who are at risk of suicide using their responses to standardized questions for depressed mood and suicide attempts, b) advise women directly if they are at-risk of suicide and provide options for managing the situation, including a follow up contact with an RA; and; c) alert RAs by email when a woman at-risk wishes to be contacted. Follow-up contact with women will be guided by a standard protocol, based on current best practices in suicide management. All research assistants will complete the Applied Suicide Intervention Skills Training (ASIST). The principal investigators at each site, who are Registered Nurses, will be available to consult with and support RAs, if needed.

### Outcomes

The primary outcomes are:
*Depressive Symptoms* measured by the Center for Epidemiologic Studies Depression Scale, Revised (CESD-R) [40]. The CESD-R is a 20-item self-report measure of symptoms reflective of the DSM-IV criteria for depression. Women rate how often they have experienced each symptom in the past week using 5 options that range from ‘not at all or less than 1 day’ to ‘nearly every day for 2 weeks’. Total and subscale scores are computed by summing responses to applicable items. The revised CESD correlates highly with the original scale, and demonstrates good to excellent face and construct validity, as well as excellent internal consistency (α = .90-.96) [40, 41].
*PTSD Symptomology*, measured on the PTSD checklist, Civilian Version (PCL-C) [42, 43]. The PCL-C is a 17 item self-report measure designed for use in community samples to assess the probability of meeting DSM-IV diagnostic criteria for PTSD. The PCL-C asks about symptoms in relation to generic stressful experiences; women rate how bothered they are by each symptom during the past month using a 5 point Likert-type scale, with a range of 1 (not at all) to 5 (extremely). Total summation score range from 17-85, with higher scores indicative of greater symptomatology. The PCL-C has demonstrated validity and excellent internal consistency reliability (.94 for the total scale and .82 to .94 for subscales) [44].

The secondary outcomes are:
*Decisional Conflict*, measured on an adapted 13 item version of the low literacy Decisional Conflict Scale (DCS) [45]. The DCS assesses the extent to which women understand the advantages and disadvantages of safety planning options and their values related to these decisions [46]. The DCS discriminates between people who make decisions and those who delay making decisions [47]. Women self-report on a 3 point Likert-type scale as to which option they prefer, ‘yes’ (0), ‘unsure’ (2), or ‘no’ (4). Scoring is summative, with higher scores representing higher levels of decision conflict and anxiety [45]. The low literacy version of the DCS has shown good test-retest reliability (.75) and internal consistency (α = .72) [47].
*Use of Safety Actions*, measured on a 22 item self-report scale, adapted from several sources, including the Safety Behavior Checklist [48], Intimate Partner Violence Strategies Index [49] and our previous longitudinal research [50]. Women are asked to indicate whether they have used a variety of safety behavior strategies/actions (yes/no) within the past 12 months and, if used, how helpful this strategy was it in dealing with the violence (on a 5-point scale ranging from ‘not at all helpful’ to ‘very helpful’).
*Mastery*, measured on Pearlin’s 7-item Mastery Scale. The Mastery Scale is a self-report measure that taps into perceptions of personal control over one’s life. Women respond to how much they agree (1 = strongly agree) or disagree (7 = strongly disagree) with each item. Scores are computed by summing responses to all items, where higher scores indicating greater perceived mastery. The Mastery Scale has demonstrated good internal consistency (α = .75 -.78) and has been widely used in a variety of populations providing evidence of strong face validity [51–53].
*Self-efficacy for Safety Planning*, measured on 2 visual analogue scales (VAS), developed for this study. Women are asked to rate their confidence in making a safety plan for themselves on a 100 mm horizontal line, with anchors of ‘not at all confident’ and ‘completely confident.” Women with children will be asked to complete a second VAS to rate their confidence in making a safety plan for their children. VAS scores are recorded by the website as the distance in mm from the left anchor (0) to the location of the mark on the line. Scores range from 0 to 100, with greater scores represent greater self-efficacy for safety planning.

Other outcomes:
*Level of Coercive Control*, measured on the Women’s Experiences with Battering (WEB) Scale [54]. The WEB is a 10-item scale designed to measure the intensity of experiences of psychological vulnerability from IPV and the impact of coercive control [54–56]. For each item, woman are asked to respond on a 6-point Likert scale, ranging from 1 (Strongly agree) to 6 (Strongly disagree). Total summation scores range from 10 to 60; lower scores represent less abusive behavior and loss of power and control. The WEB has demonstrated high internal consistency (α = .99) and construct validity [54].
*Severity of Intimate Partner Violence*, measured on the 30-item Composite Abuse Scale (CAS), asks women to rate the frequency of experiencing specific abusive acts in the previous 12 months on a 6-point scale ranging from ‘never’ (0) to ‘daily’ (5). Using cut-off scores, women’s responses are categorized as ‘positive’ or ‘negative’ for exposure to 4 types of IPV: physical abuse, emotional abuse, harassment and severe combined abuse. A total summative score can be derived, with higher scores indicative of greater severity of abuse [57]. The CAS has demonstrated good internal consistency [58] and evidence of content, construct, criterion, and factorial validity [59]. In this study, the 3 sexual abuse items were modified to make them more consistent with current theory and measurement approaches in the field [60].
*Social Support*, measured using a 5-item modified scale from the Medical Outcomes Study Social Support Survey (MOS-SSS). The shortened MOS-SSS assesses the perceived availability of emotional, informational, and instrumental support. For each item, the availability of support is rated on a 5-point Likert-type scale, ranging from 1 (none of the time) to 5 (all of the time). Total summative scores are computed, with higher scores suggestive of greater perceived support. The 5-item version has demonstrated good internal consistency (α = .87) and validity [61].

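### The stated response coding of the coercive-control scale (WEB) conflicts with the stated direction of its total, and no recoding step is given

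*Protocol article*

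**What the plan says.** All the relevant statements are in the Outcomes section of the protocol article, under the entry for level of coercive control.

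- Construct: "The WEB is a 10-item scale designed to measure the intensity of experiences of psychological vulnerability from IPV and the impact of coercive control".
- Response options and total: "ranging from 1 (Strongly agree) to 6 (Strongly disagree). Total summation scores range from 10 to 60; lower scores represent less abusive behavior".
- The sentence on the total in full: "Total summation scores range from 10 to 60; lower scores represent less abusive behavior and loss of power and control".

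No reverse-coding step is given and no item text is shown. The scale is listed under "Other outcomes", after the primary and secondary outcomes. The Data collection section has coercive control measured in both groups at each study visit.

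**The concern.** The scale measures something bad (vulnerability, the effect of being controlled), and the lowest code goes to the strongest agreement. A low total should then mean much vulnerability, but the article says that it means less abuse. Each statement is plain by itself. Together they are incompatible unless the items are reversed before summing or are all worded as absence of vulnerability, and the article says neither.

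At stake is the sign of any comparison of coercive control between arms. An analyst who added the responses as coded and then applied the stated label would report benefit as harm, or harm as benefit. In a trial that defines partner violence in terms of coercive control, that would be an awkward error even on a lower-tier measure.

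**Working it through.** **Inputs (Outcomes section).** 10 items; codes 1 (strongly agree) to 6 (strongly disagree); stated total range 10 to 60; low total read as less abuse.

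**Assumption.** Agreeing with an item endorses vulnerability. This is inferred from the stated construct, because item wording is not shown.

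**Step 1. Reproduce the stated range.**
- As coded: 10 × 1 = 10 to 10 × 6 = 60.
- Reversed, each item scored 7 − response: 10 × (7 − 6) = 10 to 10 × (7 − 1) = 60.

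The stated range reproduces both ways, so it cannot show which scoring is meant.

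**Step 2. Score the two extreme respondents.**

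| Respondent | Total as coded | Total after 7 − response | Stated meaning of the total as coded |
|---|---|---|---|
| Strongly agrees with all 10 (most vulnerable) | 10 | 60 | least abuse |
| Strongly disagrees with all 10 (least vulnerable) | 60 | 10 | most abuse |

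The stated direction fits the reversed total and contradicts the total as coded.

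**Step 3. Effect on an arm difference.** Summing 7 − response over ten items gives reversed total = 70 − total as coded. Hence

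(difference as coded) = (70 − reversed mean, intervention) − (70 − reversed mean, control) = −(difference on the reversed total).

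Size and spread are unchanged and only the sign flips. As an illustration, a true 5-point reduction would be reported as a 5-point increase.

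**Step 4. Would routine checks find it?** A range check would not (Step 1). Nor would internal consistency: replacing every item by 7 − item leaves all inter-item covariances unchanged. The check needs an outside measure of known direction. The Composite Abuse Scale is collected at the same visits, is coded 0 (never) to 5 (daily), and has higher totals for more severe abuse.

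**Step 5. Compare with neighbouring scales.** For the PTSD checklist, the Composite Abuse Scale and the social support scale, the stated codes rise in the same direction as the stated meaning of the total. The decisional conflict codes (yes 0, no 4) are also compatible with higher meaning more conflict. The WEB entry is the one where the codes run against the stated construct.

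**The case against.** The strongest reply is that the article omits a step and does not misstate one. It gives the response options and the meaning of the total, and it nowhere says that unreversed responses are added. Stating the intended direction could itself tell an analyst that recoding is needed. A condensed article may leave scoring to the instrument's instructions or to the analysis plan, and no item text is shown to prove the polarity. This much stands: a wrong sign in the actual analysis is a possibility and not a demonstrated fact. A reader might infer that the trial will report coercive control backwards. The document does not support that inference.

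The conflict on the page remains. Construct, coding, summation and direction are all stated, and on the natural reading they do not fit together. The final clause can also be read so that low totals mean less abuse but more loss of power. That reading makes the sentence contradict itself, so it is no rescue.

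A second objection concerns reach, and it stands in full. Under Examination of outcomes by study arm, the GEE tests cover mental health, decisional conflict, safety-seeking behaviour, mastery and self-efficacy. The mediators listed for the structural equation model include abuse severity, and the Outcomes section assigns severity to the Composite Abuse Scale. The WEB is named in neither place.

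A reader might also extend the point to the Mastery Scale, which is likewise coded 1 for strong agreement and described as "Scores are computed by summing responses to all items, where higher scores indicating greater perceived mastery". The document does not support that. With k of the 7 items worded as having control, adding responses as coded gives the woman with the highest mastery k × 1 + (7 − k) × 7 = 49 − 6k, and the woman with the lowest 7k + (7 − k) = 7 + 6k. The stated direction therefore holds for k up to 3, that is, whenever most items express lack of control. Saying that the scale concerns personal control names the construct and not the wording of the items. No contradiction can be shown, and a list of reversed items is detail that an article commonly leaves elsewhere.

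**Conclusion.** The concern holds for the WEB alone, as a conflict between its stated coding and the stated direction of its total. If agreement endorses vulnerability and responses are summed as coded, the most vulnerable woman receives 10, the score labelled least abuse. Every arm difference would then be interpreted with the opposite sign at unchanged size. Both conditions are needed: the first is inferred from the construct, and the article does not settle the second.

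The consequence is confined to an outcome that is neither primary nor secondary. No sample size, power or alpha figure depends on it, and no planned test or mediator named in the article uses it. The text should be corrected, but the main conclusions of the trial are not threatened.

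**What to change.** Add one scoring sentence to the WEB entry: each item is scored as 7 minus the response before summing, so that 60 represents the greatest vulnerability and lower totals represent less. If the responses are instead to be summed as coded, reverse the sentence on direction. In either case, reword the final clause so that abuse and loss of control plainly move the same way.

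Before any comparison by arm, confirm the direction on baseline data pooled over arms. The recoded WEB total should correlate positively with the Composite Abuse Scale total; a total left as coded should correlate negatively. This assumes only that more severe abuse goes with greater vulnerability.

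The cost is one sentence and one correlation on data already collected. No arm information is needed, and no other part of the plan changes.
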